**4. Causality assessment criteria:**

4.1. **Is the serious effect related to the therapy?** 1. Not related 2. Probably 3. Unlikely

4.1.1. **What is your Arguments for decision.....**

4.1.2. Remarks/Observations regarding this serious adverse effect case management.....

.....

**NOTE: Serious adverse effects will be treated and observed for 24 hours (maximum) by the physicians on the field. If there is no improvement, the subject will be transferred to the most appropriate health care facility**

Thank you for your collaboration

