### 8.4 Recording of any AE/SAEs

The study defines AEs and SAEs per the national guidelines which are also found in the Serious Adverse Events handbook created by RTI ENVISION and the Task Force for Global Health:

**“Adverse event from MDA (AE-F-MDA)** is a medical event that takes place in an MDA program, causes concern in the medical and wider community and is believed to be caused by the drug(s) used. It can be caused by either administration of the drug or by a coincidental event that by chance happened after drug administration. Most AEs-f-MDA (adverse events from MDA) are self-limiting and treatable using simple remedies and are not usually required to be reported to national or international regulatory authorities.

**Serious Adverse Event (SAE)** is a regulatory term describing any untoward medical occurrence with any of the following characteristics:

- Results in death;
- Requires in-patient hospitalization;
- Results in persistent or significant disability;
- Is life-threatening; or
- Results in a congenital anomaly/birth defect.”

All adverse events will be recorded and followed up by the nurses on the team. The reporting of adverse events will be systematic and comply with national AE/SAE reporting guidelines to avoid any bias related to the wording of the question(s).

While the difference between “adverse events” and “serious adverse events” have been described above, there is also a level of severity which the study will also monitor: “The term “severe” is often used to describe the intensity (severity) of a medical event, as in the grading “mild”, “moderate”, and “severe”; thus a severe action need not be serious.” Reported adverse events will be classified according to their intensity (none, mild, moderate, and severe).

- Mild: easily tolerated, does not interfere with daily activity,

- Moderate: uncomfortable enough to interfere with daily activity,
- Severe: precludes daily activity (Given that a “severe” adverse event includes inability to complete daily activities, it will be classified as a possible SAE for the purposes of this study.)

The evolution of older complaints will be classified as: exacerbated, ongoing, and improved or resolved/none.

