### 3.4. SAEs form between D1 and D15; use the codes 1 = Severe, 2 = Very severe

| Severe effects |                                         | Days when serious side effects occurred |    |    |    |    |    |    |    |    |    |     |     |     |     |     |     |     |
|----------------|-----------------------------------------|-----------------------------------------|----|----|----|----|----|----|----|----|----|-----|-----|-----|-----|-----|-----|-----|
|                |                                         | D0                                      | D1 | D2 | D3 | D4 | D5 | D6 | D7 | D8 | D9 | D10 | D11 | D12 | D13 | D14 | D15 | D30 |
| 4.3.1          | Angioneurotic oedema/anaphylactic shock |                                         |    |    |    |    |    |    |    |    |    |     |     |     |     |     |     |     |
| 4.3.2          | Anuresis                                |                                         |    |    |    |    |    |    |    |    |    |     |     |     |     |     |     |     |
| 4.3.3          | Seizures                                |                                         |    |    |    |    |    |    |    |    |    |     |     |     |     |     |     |     |
| 4.3.4          | Erythema multiforme                     |                                         |    |    |    |    |    |    |    |    |    |     |     |     |     |     |     |     |
| 4.3.5          | Epidermal necrolysis                    |                                         |    |    |    |    |    |    |    |    |    |     |     |     |     |     |     |     |
| 4.3.6          | Recurrent symptoms                      |                                         |    |    |    |    |    |    |    |    |    |     |     |     |     |     |     |     |
| 4.3.7          | Stevens Johnson Syndrome                |                                         |    |    |    |    |    |    |    |    |    |     |     |     |     |     |     |     |
| 4.3.8          | Others                                  |                                         |    |    |    |    |    |    |    |    |    |     |     |     |     |     |     |     |
| 4.3.9          | If other specify.....                   |                                         |    |    |    |    |    |    |    |    |    |     |     |     |     |     |     |     |

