|                | .....                                   |                                         |    |    |    |    |    |    |    |    |    |     |     |     |     |     |     |     |
|                | .....                                   |                                         |    |    |    |    |    |    |    |    |    |     |     |     |     |     |     |     |

**AFTER COMPLETING QUESTIONS UNDER 4.3 AND 4.2, THE INVESTIGATOR SHOULD ANSWER THE FOLLOWING QUESTION; THE ANSWER WILL BE YES IF ANY SEVERE EFFECT IS WAS REGISTERED**

3.5. Did the interviewed participant experience a serious/severe adverse event after taking the 3 drugs? 1. Yes 2. No 99. unknown

3.6. If yes for 4.5, please list down.....

3.7. If yes for 4.5, please complete the Fever and serious adverse events **surveillance form appendix 2.**

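### The Appendix 5 note gives non-improvement as the only explicit trigger for transfer and makes no exception for serious events that threaten life or need in-patient care

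*Protocol*

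**What the plan says.** The instruction is a note at the foot of the SAE recording form (Protocol Appendix 5, after item 4.1.2). It reads "Serious adverse effects will be treated and observed for 24 hours (maximum) by the physicians on the field" and continues "If there is no improvement, the subject will be transferred to the most appropriate health care facility". It names no other condition for transfer and no class of event to which it does not apply.

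The form covers a mixed group. Item 3.4 tells staff to "use the codes 1 = Severe, 2 = Very severe", which grades intensity. Its rows include "Angioneurotic oedema/anaphylactic shock", seizures, "Epidermal necrolysis" and "Stevens Johnson Syndrome". Item 3.5 then puts both notions into one question: "Did the interviewed participant experience a serious/severe adverse event after taking the 3 drugs".

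Section 8.4 gives five criteria that make an event serious. One is "Requires in-patient hospitalization"; another is a threat to life. The same section treats an event that is only severe, meaning that it stops daily activity, as a possible SAE.

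Section 8.7 places a study physician on site for the 14-day exercise, has nurses in regular contact with that physician, alerts a nearby hospital, and supplies three cars that can be used for evacuation. It does not say which events call for evacuation or how quickly.

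**The concern.** Some events are serious under section 8.4 precisely because they need a hospital bed or threaten life. For these, the question of whether hospital care is needed is already answered when the event is classified. The note nevertheless puts them under the same rule as a severe event that might settle in the field: treat, watch, and transfer if there is no improvement.

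That trigger fails in two ways for this group. A participant may improve somewhat after first treatment and still need a hospital. A participant who does not improve could, if the note is applied literally, spend up to 24 hours in the field first. What is at stake is the care of a small number of participants with grave events. Because the hospital and vehicles are already planned, any delay would come from how the instruction is worded or understood and not from missing resources.

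**Working it through.** No figure in the plan needs reproducing. The check sets the relevant texts side by side and then sizes the likely load.

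**1. Scope of the note.** It speaks of serious adverse effects without qualification. Items 3.4 and 3.5 show that the form collects both severe and serious events, so the rule reaches both.

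**2. Fit with section 8.4.** Two of the five seriousness criteria (in-patient hospitalization; life-threatening) describe events for which waiting to see improvement is unsuitable. For events that are merely severe, observation by a physician is reasonable. The fault is therefore the lack of a split between the two groups, not the existence of field observation.

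**3. Fit with the form's own rows.** The form names seven conditions (rows 4.3.1 to 4.3.7). On a clinical reading, at least four would usually need hospital assessment: anaphylactic shock, seizures, epidermal necrolysis and Stevens Johnson Syndrome. That classification is a judgement made here; the protocol does not make it.

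**4. Search for a rule elsewhere that would take precedence.**

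| Place | What it provides | Transfer criterion? |
|---|---|---|
| Appendix 5 note | Field care up to 24 hours, then transfer | Yes: no improvement |
| Section 8.7 | Physician, stand-by hospital, cars | General only: if evacuation proves necessary |
| Section 8.5 and the DSMB charter | Prompt review of any SAE and a DSMB call | None: the purpose is attribution and whether the board meets |
| Sections 8.4 and 8.5 | National guidelines for definitions and reporting; handbook for definitions and investigation steps | None stated in the protocol |

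So non-improvement is the only explicit transfer criterion in the document.

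**5. Likely load if transfer were immediate.** Inputs: the Mali study described in section 1.8 reported no SAE in 3,011 people; the trial targets 16,000.

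- Exact one-sided 95% upper limit: 1 − 0.05^(1/3011) = 0.0994%. Then 0.000994 × 16,000 = 15.9, about 16 events.
- Allowing for clustering by village with an assumed design effect of 2, the effective sample is 3,011 / 2 = 1,505.5, and 1 − 0.05^(1/1505.5) = 0.199%. Then 0.00199 × 16,000 = 31.8, about 32 events.

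These limits bound the number of SAEs if the Mali risk carries over. They do not estimate delayed transfers, and they leave out severe events counted only as possible SAEs. They support one statement: a rule of immediate transfer would add little work.

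**The case against.** The strongest reply is that the note should not be read alone. It is a footer on a data form, while medical access is set out in section 8.7. There the hospital is on alert for any reaction, the cars are for evacuation when it is needed, and a physician is at hand to judge that need. None of this depends on a wait or on non-improvement. The word maximum also makes 24 hours a ceiling, which limits how long a patient may be kept in the field and obliges nobody to wait. Finally, the national guidelines and the handbook are not available here and may contain referral criteria.

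Most of this stands. A reader might infer that the protocol orders staff to hold a patient in the field for 24 hours, or that a partly improved patient cannot be sent to hospital. The documents support neither: the time is a cap, and section 8.7 permits earlier evacuation. Nor can it be said that no referral criteria exist anywhere, because the external guidance is unseen.

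What the reply does not remove is the wording of the one explicit rule. Section 8.7 supplies means without saying when to use them, and the note refers neither to that section nor to the guidelines. A written safety instruction should not rely on staff recognising that it ought to be set aside for the gravest events.

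**Conclusion.** The point holds in a limited form. The only explicit transfer criterion in the protocol is unsuitable for events that section 8.4 makes serious through threat to life or need for in-patient care, and the note has no exception for them. Earlier transfer is allowed but not required.

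The size is small in number and concerns participant safety only. Two of five seriousness criteria are affected. The expected number of SAEs is low, with upper limits of about 16 to 32 in 16,000, assuming a Mali-like risk and a design effect of 1 to 2.

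Two further readings should be resisted. One is that field management would lower the SAE count or distort the comparison of arms. Section 8.4 turns on whether hospital care is required, not on whether transfer took place, and it counts severe events as possible SAEs in any case. The other is that physician cover is inadequate. Sections 8.7 and 8.8 provide a doctor throughout the distribution days, and the fault in the note is the same whoever is present.

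**What to change.** Replace the Appendix 5 note with:

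*Any event that is life-threatening or requires in-patient care (section 8.4) is stabilised and transferred at once to the stand-by referral centre in a section 8.7 vehicle, without an observation period. Other severe events may be treated and observed in the field for up to 24 hours by the study physician and are transferred if they do not improve, or earlier if hospital care is needed.*

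This keeps field observation where it is sensible and ties the exception to definitions already in the protocol. It uses the hospital and cars already planned, so it needs no extra staff or vehicles. The small cost is notifying the ethics committees of a changed form note. Appendix 1 says that the forms are to be merged into one register subject to ethics approval, so the new wording can go in at that step.

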7.1 List of contraindications to look for: 1=Yes, 2=No

| Contraindications                                                                          | 1 | 2 |
|---------------------------------------------------------------------------------------------------|----------|----------|
| 7.1.1. Pregnancy                                                                                  |          |          |
| 7.1.2. Breastfeeding                                                                              |          |          |
| 7.1.3. Children less than 5 years of age ( $\leq 90\text{cm}$ )                                   |          |          |
| 7.1.4. Allergy to one of the study drugs: azithromycin, Ivermectin, Abendazole                    |          |          |
| 7.1.5. Medicine intake: antacids containing aluminium or magnesium, nelfinavir, ergot derivatives |          |          |
| 7.1.6. Serious illness (systemic edema, severe dyspnea, etc.)                                     |          |          |
| 7.1.7. Others.....
If others, please specify:                                                  |          |          |

DECISION REGARDING INCLUSION IN THE STUDY : 1. Yes, 2. No

7.2. Concomitant Treatments: codes; 0: Not administered 1: Administered; D=day

| Concomitant Treatments                                   | D0 | D1 | D2 | D3 | D4 | D5 | D6 | D7 | D8 | D9 | D10 | D11 | D12 | D13 | D14 | D15 | D30 | code |
|----------------------------------------------------------|----|----|----|----|----|----|----|----|----|----|-----|-----|-----|-----|-----|-----|-----|------|
| Antalgic treatment: paracetamol                          |    |    |    |    |    |    |    |    |    |    |     |     |     |     |     |     |     |      |
| Anti-inflammatory treatment: diclofenac                  |    |    |    |    |    |    |    |    |    |    |     |     |     |     |     |     |     |      |
| Anti-malarial treatment: artemisin and quinine compounds |    |    |    |    |    |    |    |    |    |    |     |     |     |     |     |     |     |      |
| Antibiotics treatment: all categories                    |    |    |    |    |    |    |    |    |    |    |     |     |     |     |     |     |     |      |
| Local treatment (eyes, lymphoedema, skin, etc.)          |    |    |    |    |    |    |    |    |    |    |     |     |     |     |     |     |     |      |
| Solutes                                                  |    |    |    |    |    |    |    |    |    |    |     |     |     |     |     |     |     |      |
| Corticoids                                               |    |    |    |    |    |    |    |    |    |    |     |     |     |     |     |     |     |      |
| Cardio-stimulants                                        |    |    |    |    |    |    |    |    |    |    |     |     |     |     |     |     |     |      |
| Anxiolytics                                              |    |    |    |    |    |    |    |    |    |    |     |     |     |     |     |     |     |      |
| Antihistaminics                                          |    |    |    |    |    |    |    |    |    |    |     |     |     |     |     |     |     |      |

7.3. Concomitant Treatment: Number of days|\_\_|\_\_| days

7.4. Evolution: Favourable: 1. Yes 2. No

## Appendix 10: Charter of Data and Safety Monitoring Board (DSMB)

This charter is for the DSMB for the “Comparison of the co-administration of azithromycin, albendazole and ivermectin versus standard treatment regimens during mass drug administration (MDA) in Ethiopia: a cluster-randomized trial.” This study will be conducted in Ethiopia.

The Charter will define the Terms of Reference (ToR) for the DSMB, its membership, its relationship with other trial components, and the purpose and timing of its meetings. The Charter will also provide the procedures for ensuring confidentiality and proper communication, the monitoring guidelines to be implemented by the DSMB, and outline of the content of the Reports that will be provided to the DSMB.

### ***Terms of Reference (ToR)***

1. The DSMB for the Co-administration trials are charged with the safety and well-being of the study participants. They also serve as advisors on maintaining data quality and unanticipated study events.
2. The study will generate real time analysis of the data collected and reports including rates and confidence intervals (See **Section 8.9**). As a safety measure, the study leaders will convene an immediate teleconference with the DSMB given the following criteria:
  - IF the rate of adverse events ranked as mild/moderate by participants differs significantly in the trial group as compared to the control group during the first two “Follow-up Days” (**Day 2, Day 4**) as well during subsequent review of the data at **Day 15**, and at the conclusion of the study on **Day 31** (to determine if the remainder of the woreda can safely be treated via triple drug therapy).
  - IF an SAE occurs all related data will be provided to the DSMB members who will make an initial decision about attribution and whether a formal DSMB meeting is required. (Note: Given that a “severe” adverse event includes inability to complete daily activities, it will be classified as a possible SAE for the purposes of this study.)
  - At conclusion of the study on **Day 31** (to determine if the remainder of the woreda can safely be treated via triple drug therapy).
3. If the DSMB concludes that there is evidence that warrants stopping the trial or a change in the procedures of the clinical trial, the Board will be responsible for drafting a report of their recommendations to the Principal Investigators and to the IRB of the LSHTM and AHRI. If there is no concern, the Board will also issue a report stating they have no concerns.
4. The DSMB shall meet by phone at Day 31 regardless of the occurrence of AEs and SAEs for the purposes of reviewing the accumulated data, the quality of the information collected the safety of the trial procedures and the efficacy of the treatment arms. The committee shall issue a summary report, which will be forwarded to the Co-administration study PIs, the Federal Ministry of Health of Ethiopia, and the LSHTM and AHRI IRB.
5. The location of the trial is in rural Africa. Social, cultural, or political exigencies may arise that may affect the trial or call into question some of the protocols of the trial. The DSMB has accepted the responsibility to serve as a review body for such matters, if requested by members of the DSMB or members of the study team. The members of the DSMB may request

a review by the full committee of any events arising from the study which, in the opinion of the committee member, is a serious issue or one in which a response to a government may be necessary. A conference call would be organized as expeditiously as possible with a quorum of members. For this purpose, a quorum is considered three of the five members. The call must include the Principal Investigator and the relevant study director. The committee will recommend a course of action to the Principal Investigator regarding any such events. If the study leadership does not concur with the DSMB's recommendation, it will be the responsibility of the study leadership and DSMB Chair to reach a mutually acceptable decision. A minority report will be issued from this group.

### ***DSMB Key Responsibilities***

The DSMB will be responsible for carrying out the following responsibilities:

1. Assessing data quality, including completeness.
2. Monitoring reports of recruitment and losses to follow-up.
3. Monitoring reports of the compliance with the treatment protocol by communities and investigators.
4. Monitoring evidence for intervention differences in the main outcomes.
5. Monitoring the safety of interventions (e.g., adverse events).
6. Deciding whether to recommend that the trial continues as planned or whether treatment should be terminated at the time of the interim analysis.
7. Reviewing proposed major modifications to the study prior to their implementation (e.g., increasing target sample size).
8. Suggesting additional data analyses if deemed ethically necessary.
9. Reviewing the interim stopping rule analysis prepared by the study, and communicating the result of that analysis to the PI and executive committee.

### ***Conflicts of Interest***

The DSMB membership is restricted to individuals free of apparent significant conflicts of interest. The source of these conflicts may be financial, scientific or regulatory in nature. Thus, DSMB members may not be involved in the Co-administration trial, have a vested interest in its outcome, have close personal or professional ties to a Co-administration trial investigator, or have financial investments in any of the pharmaceutical companies donating the drug. If at any time a DSMB member perceives that he/she or another member of the Board has a potential conflict of interest, he/she is obligated to bring the issue to the attention of the full DSMB for open discussion and resolution. Any DSMB members who develop significant conflicts of interest during the course of trial should resign from the DSMB. A replacement will be considered.

DSMB members will complete a conflict of interest disclosure form in advance of the first meeting. Competing interests should be disclosed by all DSMB members. The completed forms will be reviewed by the DSMB Chair. If a significant conflict of interest is noted, the DSMB Chair will determine if a member has a conflict of interest that would compromise their ability to serve on the DSMB. If he recommends resignation, the member will be replaced.

The DSMB membership is to be constituted for the duration of the Co-Administration trial. Before the publication of Co-Administration trial primary results, the DSMB members should not discuss issues from their involvement in the trial.

